### Sample Size Calculation

Our a priori power analysis using G^*^Power (78) focused on the main hypothesis of a greater reduction of BDD symptoms in the main outcome measure from pre- to post-intervention in the ImaginYouth than in the SOT group. Thus, we calculated the number of participants necessary to test the interaction effect in a 2 (intervention type) × 2 (repeated measures assessment point) analysis of variance.

The power analysis was based on α= 0.05 and 1-β= 0.95, and an effect size of *f* = 0.36 [yielded by a meta-analysis on effects in internet-based intervention studies in youth by (32)]. The resulting total sample size is *n* = 28. Taking into account expected dropouts [about 30% in internet-based studies; (79)], we aim to recruit 20 patients per study arm type.

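### The stated 95% power holds only for a between-arm difference in change of about 1.44 SD, and the article does not show that its cited source supports an effect that large

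*Protocol article*

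**What the plan says.** In the Protocol article, under Sample Size Calculation, the power analysis "focused on the main hypothesis of a greater reduction of BDD symptoms in the main outcome measure from pre- to post-intervention" in the CBT arm compared with supportive therapy. The authors sought the number of participants "necessary to test the interaction effect in a 2 (intervention type) × 2 (repeated measures assessment point) analysis of variance". The inputs are given in one sentence: "The power analysis was based on α= 0.05 and 1-β= 0.95, and an effect size of *f* = 0.36". The effect size is described as "yielded by a meta-analysis on effects in internet-based intervention studies in youth". The result is "The resulting total sample size is *n* = 28", and an expected dropout of "about 30% in internet-based studies" raises the recruitment target to 20 per arm.

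Statistical Methods plans the matching analysis, a repeated-measures ANOVA of condition by pre-post change in the primary outcome. The section does not give the pooled effect behind f, how it was converted, the G\*Power effect-size option, the pre-post correlation, or the between-arm difference that f = 0.36 represents.

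**The concern.** Cohen's f does not mean the same thing in every design. For two independent groups, f = d/2, so f = 0.36 stands for d = 0.72. In G\*Power's default setting for a within-between interaction with two arms and two time points, f is the size of each of the four interaction cell effects in SD units, and the same 0.36 stands for a difference in change twice as large. A value taken from a meta-analysis on the first scale and entered on the second would make the required sample far too small for the effect that the source supports.

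The superiority comparison is the trial's main hypothesis. If 95% power is quoted without the effect it refers to, a non-significant result could be taken as good evidence against the intervention when the trial had little chance of detecting a more ordinary benefit.

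**Working it through.** **Inputs.** From Sample Size Calculation: α = 0.05, target power 0.95, f = 0.36, a 2 × 2 interaction, total n = 28, dropout about 30%, 20 per arm. Assumed here because not stated: pre-post correlation ρ = 0.5, equal SDs at both time points, equal baseline means.

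**Step 1: reproduce the plan's figure.** For the interaction with m = 2 time points in G\*Power's default convention, the test is a noncentral F with df = (1, N − 2) and

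λ = f² × N × m / (1 − ρ).

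With ρ = 0.5, λ = 0.36² × N × 2 / 0.5 = 0.5184 × N.

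- N = 26: power 0.941
- N = 28: λ = 14.5, power 0.956

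So N = 28 is the smallest even total reaching 0.95. The dropout step also checks: 28 / 0.70 = 40.

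Other settings do not give 28:

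| Setting | N required |
|---|---|
| Default, ρ = 0.3 | 38 |
| Default, ρ = 0.7 | 18 |
| One-sided equivalent, ρ = 0.5 | 24 |
| Between-factor main effect, ρ = 0.5 | 78 |
| Effect size 'as in Cohen' option | 104 |
| Effect size 'as in SPSS' option | 106 |

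**Step 2: what f = 0.36 means on that scale.** The four interaction cell effects are ±0.36 SD. The difference between arms in pre-post change is therefore 4 × 0.36 = 1.44 outcome SD. The SD of change is √(2(1 − ρ)) outcome SDs, which equals 1 at ρ = 0.5, so 1.44 is also in units of the SD of change. Check as a two-sample t test on change with 14 per arm: 1.44 × √(14/2) = 3.81, and 3.81² = 14.5 = λ. A simulation of 20,000 trials gave power 0.956.

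**Step 3: the usual two-group meaning.** d = 2f = 0.72. With equal baselines this is a difference in change of 0.72 SD, an interaction f of 0.72/4 = 0.18. In terms of the difference D in outcome SDs, λ = D² × N / (8(1 − ρ)).

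At ρ = 0.5: N = 28 gives λ = 3.63 and power 0.45 (simulated 0.446); N = 40 gives λ = 5.18 and power 0.60. Power of 0.95 needs N = 104 analysed.

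Varying the unstated correlation with D = 0.72:

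| ρ | Power, N = 28 | Power, N = 40 |
|---|---|---|
| 0.3 | 34% | 47% |
| 0.5 | 45% | 60% |
| 0.7 | 66% | 82% |

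**Step 4: range over the unseen source effect, ρ = 0.5.**

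| Difference in change | Power, N = 28 | Power, N = 40 |
|---|---|---|
| 0.36 SD | 15% | 20% |
| 0.72 SD | 45% | 60% |
| 1.0 SD | 72% | 87% |
| 1.2 SD | 86% | 96% |
| 1.44 SD | 96% | 99% |

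The difference detectable with 95% power at ρ = 0.5 is 1.42 SD with 28 and 1.17 SD with 40.

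**Step 5: sensitivity with f as entered.** Keeping the interaction f at 0.36, power at N = 28 is 87% at ρ = 0.3 and 74% at ρ = 0, so the unstated correlation matters even if the effect is accepted.

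**The case against.** The strongest reply is that nothing has been miscalculated. With the stated inputs and a correlation of 0.5, the software returns 28 and the power is 0.956. That stands, and a reader who infers that the 95% is an arithmetical error would be wrong.

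A second tempting inference is that the authors doubled the source effect when they entered it. The article does not establish this. It shows no d or g and no conversion, and it does not say whether the pooled effect was between groups, pre-post or an interaction contrast. The value 0.72 appears nowhere in it. If the source effect were about 1.44 SD, the 95% would be sound; if 0.36 were itself the pooled d, power would be lower still, at 15% with 28. This is why a range is given and no single true power is claimed.

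It is also fair to say that a condensed article often leaves software settings to the full protocol, and that the trial is presented as a first study of feasibility and efficacy and will report Cohen's d. The unstated correlation alone would be a minor point.

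What these replies do not answer is that the article itself publishes a power figure, and that this figure requires a 1.44 SD advantage. The comparator is supportive therapy with weekly therapist contact, which the Discussion expects may itself bring improvement. Nothing in the article supports a difference that large, and the reader is not told that it is being assumed.

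**Conclusion.** The point holds in conditional form. The 95% power at n = 28 is correct for the effect entered, but that effect is a between-arm difference in change of about 1.44 SD, which is neither disclosed nor tied to the cited source. On the ordinary reading of a two-group f, the effect is 0.72 SD and power is about 45% with 28 completers and 60% with all 40. No correlation from 0.3 to 0.7 brings it near 95%: the highest value is 82%, with all 40 analysed at ρ = 0.7. At ρ = 0.5, imputing dropouts for the intention-to-treat analysis cannot lift power above the 60% for 40 complete cases.

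These figures rest on equal SDs and equal baselines, on the planned repeated-measures ANOVA, and on d = 2f. The last is the standard conversion, but here it is an inference because the pooled effect is not shown.

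**What to change.** Keep N = 40 and rewrite the sample-size paragraph:

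- Give the source effect as a standardised mean difference and say what it contrasts.
- Show its conversion to the interaction scale (for example, d = 0.72 becomes interaction f = 0.18).
- State the G\*Power effect-size option and the assumed pre-post correlation.
- Restate the power for that effect at 28 and at 40 analysed. Alternatively, state that 95% power holds only for a difference of about 1.4 SD (28 completers) or 1.2 SD (40 analysed).
- Commit to interpreting a non-significant superiority result by its confidence interval.

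The cost is rewording and, unless the source effect proves to be about 1.4 SD, a less favourable stated power. No patients are added and the planned analysis does not change.

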## Discussion

The aim of this two-arm randomized controlled trial is to evaluate the efficacy of an internet-based therapist-guided CBT intervention (ImaginYouth) and its superiority over SOT for BDD in adolescents. Furthermore, we aim to assess the stability in terms of both efficacy and superiority over a period of 4 weeks post-intervention, as well as the acceptability and feasibility of the intervention format. It is hypothesized that ImaginYouth will reduce primary and secondary BDD symptoms from pre- to mid-, post-, and follow-up assessments. We further expect the reduction of primary and secondary BDD symptoms to be larger in the ImaginYouth group compared to the SOT group from pre- to mid-, post-, and follow-up assessment. Additionally, we hypothesize that the number of remitted patients and repsonders at post-assessment will be higher in the ImaginYouth than in the SOT intervention group.

ImaginYouth provides participants with a CBT-based intervention which makes use of techniques that are currently the first-line treatment recommended in adults (80, 81) and have shown first efficacy in youth as well (82). The ImaginYouth intervention removes some of the treatment barriers which young individuals with BDD might face. Particularly, it might not involve as many feelings of shame. Even though participation is not completely anonymous, contact with study staff (diagnostician and study therapist) do not need to involve personal face-to-face contact. We nevertheless decided in favor of a therapist-guided intervention as guidance has also been shown to increase adherence rates in internet-based interventions (83). ImaginYouth consists of interventions on cognitive, emotional, and behavioral levels, as do treatment manuals for BDD (34, 35). Thus, effects of the intervention should be perceived and measured on all levels (see secondary measures). Moreover, as previous online CBT interventions in BDD have shown (33), effects can also be measured with regard to comorbid psychopathology (e.g., a decrease in depressive symptoms as a consequence of reduced social withdrawal or cognitive restructuring of negative thoughts).

The current design has several advantages and disadvantages. We decided in favor of an older adolescent sample mainly in order to test the intervention in individuals who are able to participate in the trial independently of their caregivers and of their own volition, in order again to limit feelings of shame when having to ask caregivers for permission. Nevertheless, in the future, the intervention could be adapted for younger adolescents and children and also expanded to be suitable for caregivers. Furthermore, we chose a randomized controlled design with an active instead of a waitlist control group, which has the advantage that we will be able to closely monitor and attend to participants in the control group. This is important as, like in other internet- and mobile-based interventions, safety management is difficult to perform, and we have tried to combat this by preparing a multilevel anti-suicidality approach. Another advantage is that participants in SOT will already receive some help that might lead to improvement, allowing unspecific working mechanisms to be controlled for. While we cannot assess long-term stability with the current design with a follow-up period of 4 weeks, the aim of the study is to assess, for the first time, the short-term efficacy in youth with BDD and to allow participants in the SOT condition to cross over to the ImaginYouth condition swiftly. Furthermore, we decided in favor of non-standardized messages after each session of ImaginYouth (and during the SOT) by the therapist, with the therapist instead adapting her comments to the patients. While this might limit generalizability, it might on the other hand decrease dropouts. And lastly, video but not audio recording during the diagnostic sessions will be non-mandatory, as this might hinder potential patients from participating. Thus, we cannot use this option to completely rule out any objective facial flaws in appearance (if other flaws are primary video recording would not be helpful anyway).

## Conclusion

To conclude, this internet-based therapist-guided CBT intervention is a treatment that aims to reduce symptoms in adolescents with BDD. Given the scarcity of intervention research in adolescents with BDD, this study will start to close this research gap, illustrating the efficacy of CBT and superiority over supportive therapy in adolescents with BDD, as well as providing information on the acceptability and feasibility of the online format. This format might be especially ideal when targeting this population, as it can be used independently of place and time, by affected individuals who are highly tech-savvy. Furthermore, it might make treatment for BDD more accessible despite high experiences of shame in youth with BDD, and in view of the current limited availability of high-quality treatment as well as long waiting lists.
